### First Study: Development of a Gamified Web App

#### Objective

The objective is to develop a gamified web app co-designed by the research team and potential users.

#### Method

This study uses a participatory action approach, using focus groups to explore the perspective of potential users and ensure high usability and adherence. Participants include 10 cannabis-tobacco users or former users selected from 3 substance abuse programs (SAP) in Barcelona province, based on purposive sampling and inclusion criteria of 18 years of age or older, undergoing treatment for cannabis use, and owning a smartphone. The focus groups consist of 5 participants, homogeneously grouped by sex and age profiles, with sessions lasting 60 to 90 minutes. Both focus groups and participatory activities are conducted, engaging participants in-person discussions and interactive activities while recording conversations for analysis. Each group is led and coordinated by 3 individuals, including an expert in qualitative research, a web app developer, and a project investigator member.

#### Recruitment

Purposive sampling is used to recruit participants meeting the inclusion criteria. The eligibility criteria are determined by the clinicians of the SAP centers that collaborate in the study.

#### Data Collection Technique

Focus groups and participatory activities, were used, consisting of 2 pilot sessions (where a homemade board game was used to explore participants’ gaming preferences), and 3 participatory sessions (including 2 exploratory sessions with clinicians and former cannabis users to profile this population, and a third session of in-depth interviews to explore into participants’ personal experiences overcoming cannabis use). These sessions were conducted to gather pertinent information for web app design. Each session involved discussions among participants to explore various themes, such as users’ experiences with gamified web apps, expectations and preferences regarding app features, preferred game types, and personal experiences related to cannabis use.

#### Data Analysis

Transcriptions of focus group discussions and participatory activities serve as primary data for analysis, involving familiarization, coding, theme development, data interpretation, and validation. The thematic categorical content analysis will be conducted using ATLAS.ti (ATLAS.ti Scientific Software Development GmbH). Based on these findings, a web app prototype is developed.

#### Design of the Web App

With input from participating groups, an external company experienced in gamified web app design, along with patients and researchers, designs the web app prototype. The prototype incorporates variables of interest in an engaging manner. The same participants involved in co-design will pilot the web app.

### Second Study: Monitoring Patterns of Cannabis and Tobacco Use Among a Cohort of Cannabis Users Searching for Treatment

#### Objective

The aim is to monitor patterns of use of cannabis and tobacco, withdrawal symptoms, abstinence, and other indicators among cannabis users.

#### Method

This study uses a prospective longitudinal follow-up approach. The inception cohort consists of cannabis users attending SAP centers in the province of Barcelona during 2023 to initiate treatment for their disorder.

#### Eligibility for Centers and Clinicians

All SAP coordinators in the province of Barcelona (48 centers) are contacted. We plan to recruit 10 to 14 centers, each recruiting 8 to 12 participants on average.

#### Recruitment

Clinicians recruit individuals who have commenced reducing or quitting cannabis use attending in SAP. Participants are invited to self-manage and self-report their cannabis-tobacco use and symptomatology through a gamified web app and an external software that sends questionnaires regularly (every 6 days) to monitor other behavioral and contextual aspects. Before launching the study, the recruitment protocol is piloted in 3 SAP centers to make necessary adjustments for ease of recruitment by clinicians and increased acceptability among eligible participants.

#### Cohort Members

The cohort members are cannabis users beginning treatment for CUD at SAP centers in Catalonia.

#### Inclusion Criteria

Participants must be older than 18 years of age, daily cannabis users regardless of tobacco consumption pattern or type, in treatment for cannabis use or another substance in an SAP, followed by collaborating clinicians, own a smartphone or computer with an internet connection, commit to daily participation in the web app for 6 weeks, have and use WhatsApp (Meta Platforms) and email, and provide informed consent.

#### Exclusion Criteria

Individuals unable to guarantee 6 weeks of follow-up, those without access to a device for 6 weeks, inability to read and understand Spanish, and moderate or severe cognitive limitations and severe psychopathology, which will be assessed by clinicians during consultation at the time of participant invitation.

#### Sample Size

According to a recent meta-analysis, the probability of cannabis cessation in this patient population treated using diverse therapeutic approaches is relative risks (RR)=1.48 (28). Given its heterogeneity, we will use a more conservative estimate (RR=1.20). Thus, with an alpha risk of 0.05, a beta risk of 0.20 in a bilateral contrast, and accounting for 20% losses to follow-up, 282 participants will be required. Approximately 2000 people start treatment for cannabis use each year in Catalonia [28], making it feasible to recruit 282 participants within a 1-year period.

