Moreover, dual cannabis-tobacco use entails a nuanced description of dependence diagnosis for both substances collectively and individually, alongside the emergence of withdrawal symptoms, particularly when cannabis consumption is reduced or halted [7-9]. Cannabis withdrawal symptoms typically manifest within 2 to 4 days after a reduction or cessation of consumption, peak during the first week, and may persist for up to 4 weeks [10]. The cannabis withdrawal syndrome is recognized and included in the *DSM-5* (*Diagnostic and Statistical Manual of Mental Disorders* [Fifth Edition]) [11]. It is characterized by symptoms such as irritability, anger or aggression, nervousness or anxiety, sleep difficulties (eg, insomnia and disturbing dreams), decreased appetite or weight loss, restlessness, depressed mood, and at least one of the following physical symptoms causing significant discomfort: abdominal pain, shakiness or tremors, sweating, fever, chills, or headache. The symptoms can be assessed using the “Cannabis Withdrawal Checklist” scale. While this scale has been validated [12] and used primarily in English-speaking populations [13-16], its applicability elsewhere warrants consideration.

A meta-analysis has estimated that 47% of cannabis users experience withdrawal syndrome upon cessation, with its occurrence often linked to tobacco use [9]. Additionally, the severity of the cannabis withdrawal syndrome inversely affects the likelihood of successful cessation, with more severe symptoms correlating with lower rates of quitting [9]. Given that cannabis withdrawal syndrome frequently contributes to relapse [17], resulting in modest rates of abstinence maintenance, it is noteworthy that only 30% of individuals who undergo treatment manage to sustain abstinence during the initial month [18]. Various factors contribute to relapse, including the use of other psychoactive substances [19], psychological variables (emotions, social pressure, etc), perceptions of social norms, self-efficacy [20], and sociodemographic variables (sex, age, ethnicity, etc) [16].

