## Methods

### Project Design

The project adopts a sequential mixed methods research design encompassing 3 studies. The first study, a qualitative participatory action study aimed at addressing objective 1 by exploring key elements pertinent to the co-design of the gamified web app. The second study is a prospective longitudinal (cohort) study targeting objectives 2 to 5 to quantitatively examine implementation and effectiveness outcomes. The third is a qualitative phenomenological study addressing objective 6 to delve into participants’ experiences within the project. This integrated approach enables a comprehensive investigation into the patterns of consumption and withdrawal syndrome associated with dual cannabis and tobacco use among individuals undergoing cessation treatment for CUD, synthesizing qualitative insights with quantitative findings to provide a holistic understanding of the research objectives.

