#### Statistical Methods

For independent variables, a descriptive analysis will be conducted, including frequencies, percentages, and their 95% CIs. To assess effectiveness measures such as changes in cannabis-tobacco use, withdrawal syndrome, and treatment adherence, frequencies and percentages will be described for baseline and main assessment end points according to the four patterns of cannabis use and they are (1) concurrent, (2) sequential concurrent, (3) asynchronous concurrent, and (4) exclusive cannabis. Incidence rates of abstinence and symptomatology will be calculated for the same assessment end points across the 4 patterns. The RR of quitting or reducing cannabis and tobacco, as well as quit attempts for both substances (95% CI), adjusted for independent variables, and initial consumption pattern, will be calculated using Cox or Poisson robust regression models. Predictive analysis techniques including logistic regression and random forest will be used to model the probability of events occurring based on other factors. Time series analysis will be used to observe consumption trends during the follow-up, and survival analysis of recurring events will be conducted to observe abstinence or reduction processes among participants.

For all analyses, SPSS (IBM Corp) for Windows version 21, Python (version 3; Python Software Foundation), R (version 4.0.3; R Core Team), and scikit-learn will be used. The level of significance will be set at 5% (*P*<.05).

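### The 282 participants cannot be reproduced from RR=1.20 at the only abstinence rate in the article (30%), and that RR is tied to no comparison the cohort will analyse

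*Protocol article*

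**What the plan says.** In the protocol article, Sample Size starts from a meta-analysis and states that "the probability of cannabis cessation in this patient population treated using diverse therapeutic approaches is relative risks (RR)=1.48". It then discounts this: "Given its heterogeneity, we will use a more conservative estimate (RR=1.20"). The error rates are given as "with an alpha risk of 0.05, a beta risk of 0.20 in a bilateral contrast", and the result is that, "accounting for 20% losses to follow-up, 282 participants will be required". The section states no reference risk, outcome definition, groups to be compared or allocation.

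The only abstinence rate in the article is in the Introduction, under Cannabis and Tobacco Use: "only 30% of individuals who undergo treatment manage to sustain abstinence during the initial month".

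On design, Project Design says: "The second study is a prospective longitudinal (cohort) study targeting objectives 2 to 5". Cohort Members adds: "The cohort members are cannabis users beginning treatment for CUD at SAP centers in Catalonia". Statistical Methods describes results "according to the four patterns of cannabis use" and plans covariate-adjusted RRs for quitting, reducing and quit attempts. Objective 3 separates participants by whether they receive help to stop tobacco.

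The enrolment target in the Abstract (Results) and in the Results section for the second study is 150, not 282.

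**The concern.** A relative risk is not a probability. To turn one into a sample size, a reference risk and two groups are needed, or a fixed benchmark for a one-sample test. The section gives neither, but still presents 282 as following from its inputs.

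Two problems follow. First, when the missing reference risk is filled with the one abstinence rate the article reports, the answer is far from 282. Second, the RR of 1.48, and so its discounted value of 1.20, is worded as what therapeutic approaches achieve. All members of this cohort are in treatment, so no treated-versus-untreated contrast is available, and the section does not attach RR=1.20 to any contrast that is.

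At stake is how the results are read. A reader told that the study has 80% power for RR=1.20 could take a null RR as evidence of no association, when on the article's own rate the study may have had little chance of finding one.

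**Working it through.** **Inputs.** From Sample Size: two-sided alpha 0.05 (z = 1.960), power 0.80 (z = 0.842), RR 1.20, losses 20%, N = 282. From the Introduction: reference abstinence p0 = 0.30, so p1 = 1.20 × 0.30 = 0.36. The 1:1 split is my assumption and the most favourable to the plan among the allocations tried.

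**The plan's own figure.** It cannot be reproduced from the section's inputs alone, because no reference risk is stated. The steps below supply 30%, then solve for the rate that 282 would need.

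**Two-sample comparison, 30% vs 36%.** Pooled formula:

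n per group = [1.960·√(2·p̄(1−p̄)) + 0.842·√(p0(1−p0) + p1(1−p1))]² / (p1−p0)², with p̄ = 0.33

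= [1.960 × 0.6650 + 0.842 × 0.6636]² / 0.06²
= (1.3034 + 0.5585)² / 0.0036
= 3.467 / 0.0036 = 962.9, so 963.

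Total evaluable: 2 × 963 = 1,926. Enrolled: 1,926 / 0.80 = 2,407.5, so 2,408. Ratio to the plan: 2,408 / 282 = 8.5.

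**Power with 282 enrolled.** Evaluable: 282 × 0.80 = 225.6, or 112.8 per group.

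Power = Φ[(0.06 × √112.8 − 1.3034) / 0.6636] = Φ[(0.637 − 1.303) / 0.6636] = Φ(−1.00), about 0.16.

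Solving the same formula for p1 at 112.8 per group gives a detectable RR of about 1.60 (30% vs about 48%). That exceeds even the undiscounted 1.48.

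**One-sample test against a fixed 30%.**

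n = [1.960·√(p0(1−p0)) + 0.842·√(p1(1−p1))]² / (p1−p0)² = (0.898 + 0.404)² / 0.0036 = 471.

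Enrolled: 471 / 0.80 = 588.75, so 589, about 2.1 times 282.

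**Other variants at 30%.**

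| Variant | Evaluable | Enrolled (N/0.80) |
|---|---|---|
| Two-sample, one-sided | 1,518 | 1,898 |
| 30% as the higher rate (25% vs 30%) | 2,502 | 3,128 |
| Log-RR formula | 1,942 | 2,428 |
| Allocation 1:2 (smallest of the unequal splits tried) | 2,153 | 2,692 |
| One-sample, one-sided | 373 | 467 |
| RR 1.48 in place of 1.20, two-sample | 352 | 440 |

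A hazard ratio of 1.20 with equal groups would need about 945 events, more than the number of participants. None of these gives 282.

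**Reference rate that 282 would need (RR 1.20, two-sided, N/0.80).**
- Two-sample, 282 as the total (112.8 evaluable per group): about 73%.
- Two-sample, 282 per group (225.6 evaluable per group): about 62%.
- One-sample (225.6 evaluable): about 46%.

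The article gives none of these as an abstinence rate. The 47% in the Introduction is the share of users with withdrawal syndrome, not abstinence.

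**Sensitivity of the two-sample total enrolled to the reference rate.** About 4,200 at 20%, 2,408 at 30%, 1,510 at 40%, 970 at 50% and 610 at 60%.

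**At the target of 150.** Evaluable: 150 × 0.80 = 120, or 60 per group. At 30% and 1:1, power for RR 1.20 = Φ[(0.06 × √60 − 1.3034) / 0.6636] = Φ(−1.26), about 0.10. The detectable RR is about 1.83.

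**The case against.** The strongest reply is that Sample Size never uses the 30%. That rate is in the Introduction and describes sustained abstinence in the first month, an outcome the sample-size section does not name. Statistical Methods also covers reducing use and quit attempts, which may be more common and for which the article gives no rate. This stands. It would go too far to say that the authors planned on 73%, or that 282 is a proven slip of arithmetic: the inputs are incomplete, and on a one-sample reading 282 would correspond to about 46%.

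It also stands that 16% is not the power of the planned analyses as a whole. It applies to one binary abstinence contrast with equal groups, while Cox and recurrent-event models are planned too.

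A reader might infer that the study has no comparison group at all. The article does not support that: there are contrasts by use pattern and by help to stop tobacco. What is lacking is a treatment comparator and any link from RR=1.20 to those contrasts. That 1.48 is a treated-versus-control ratio is itself read from the article's wording; the cited meta-analysis was not available.

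A reader might also tie this to the article's effectiveness wording. That is a separate matter, since no causal claim rests on the 282.

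Finally, an article may leave design details to a fuller document, so the omissions alone would not count. But this article presents a derivation with a formal power claim, and the one rate it reports does not support that claim.

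**Conclusion.** The sample-size statement is unsupported as written. It cannot be reproduced from its stated inputs, and no calculation tried at the article's only abstinence rate gives 282. The size of the gap depends on the assumed design. For a 1:1 two-sample abstinence contrast at 30%, about 2,408 enrolled are needed against 282, with about 16% power at 282. For a one-sample two-sided test against 30%, the need is about 589. The most lenient version tabulated, one-sample and one-sided, still needs about 467 and departs from the two-sided test the section specifies. Unequal use-pattern groups would raise the two-sample figure further.

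Separately, RR=1.20 is attached to no comparison in the study. The objectives of the second study are largely to describe, validate and predict, so the study does not stand or fall on this number. The claim of 80% power for RR=1.20 should still not stay in the article.

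**What to change.** Rewrite the Sample Size paragraph:

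- Remove the claim of 80% power for RR=1.20.
- Name a contrast the study will analyse (by use pattern, or by help to stop tobacco, for example), with its outcome and the assumed group split.
- State the reference rate, for example 30% with a range around it.
- Report the detectable RR, or the expected confidence interval width, at the N actually targeted. Say which N that is, because Sample Size gives 282 while the Abstract and Results give 150. Under 1:1, 30% and 20% losses, the detectable RR is about 1.60 at 282 and about 1.83 at 150.
- If the aim is mainly descriptive, base the justification on precision alone.

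The cost is one paragraph of text and a short calculation. No additional enrolment is asked for. The downside is that the stated figure becomes less favourable.

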**Results:**

By June 2024, the project had completed the first study, defining eligible cannabis user profiles, developed the initial web app prototype, and initiated recruitment across 10 centers, with 74 participants enrolled, aiming to reach 150 participants in total.

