### Second Study: Monitoring Patterns of Cannabis and Tobacco Use Among a Cohort of Cannabis Users Searching for Treatment

Recruitment efforts have commenced across 10 centers, with 74 participants enrolled to date. We anticipate reaching our target enrollment of 150 participants shortly (see Figure 2). This longitudinal prospective study will track participants’ cannabis-tobacco usage patterns, types and frequencies of tobacco use, nicotine dependence levels, withdrawal symptoms, psychoemotional factors, and motivation to quit both substances over a 6-week period.

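### The sample-size section requires 282 participants for 80% power, but the enrolment target is 150 and the site plan gives about 80 to 168, so the stated power is not delivered

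*Protocol article*

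**What the plan says.** All the relevant statements are current text of the protocol article and concern the second study.

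- **Sample Size.** The assumed effect is RR 1.20, chosen as more cautious than a meta-analytic 1.48. The error rates are a two-sided alpha of 0.05 and a beta of 0.20. The resulting size is given as follows: "accounting for 20% losses to follow-up, 282 participants will be required". The section then cites about 2000 treatment starts a year in Catalonia and draws this conclusion from them: "making it feasible to recruit 282 participants within a 1-year period".
- **Eligibility for Centers and Clinicians.** All 48 centers in Barcelona province are contacted, and "We plan to recruit 10 to 14 centers, each recruiting 8 to 12 participants on average".
- **Abstract, Results.** The study stood in June 2024 "with 74 participants enrolled, aiming to reach 150 participants in total".
- **Results, Second Study.** "We anticipate reaching our target enrollment of 150 participants shortly".

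No section says that the requirement was revised, why 150 replaced 282, or what power or precision 150 provides. The Sample Size section does not name the groups compared, the abstinence rate in the reference group, or the split between groups.

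**The concern.** A requirement of 282 and a total target of 150 cannot both describe this cohort. The 150 is not an interim milestone: the Abstract gives it as the total, and the interim count is 74.

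What is at stake is the power statement. Statistical Methods plans adjusted relative risks of quitting or reducing at the 5% level. Someone who checks the Sample Size section to judge an inconclusive relative risk will find 80% power for RR 1.20. The study that is being recruited does not have that power, even on the protocol's own reckoning.

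**Working it through.** **Inputs from the article.** RR 1.20; two-sided alpha 0.05 (z = 1.96); power 80% (z = 0.8416); 20% losses; required N 282; target N 150; 10 to 14 centers averaging 8 to 12 each; 74 enrolled in 10 centers by June 2024.

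**Step 1. Can 282 be reproduced?** Not from the stated inputs, because a two-proportion calculation needs a reference rate and a split. Assuming equal groups, with the usual pooled formula

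n per group = [1.96·√(2p̄(1−p̄)) + 0.8416·√(p0(1−p0) + p1(1−p1))]² / (p1−p0)², with p1 = 1.2·p0,

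and N = 2n/0.8:

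| Assumed p0 | p1 | Evaluable | Enrolled |
|---|---|---|---|
| 0.30 | 0.36 | 1926 | 2408 |
| 0.50 | 0.60 | 776 | 970 |
| 0.733 | 0.88 | 226 | 283 |

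So 282 corresponds to a reference rate near 73% if the groups are equal. The article gives no such rate. The next steps therefore take 282 at face value as the size that gives 80% power.

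**Step 2. What the site plan gives.** 10 × 8 = 80 and 14 × 12 = 168. The target of 150 lies inside this range; 282 does not. Reaching 282 would need 282/14 = 20.1 participants per center with 14 centers, or 282/10 = 28.2 with 10, against a planned average of 8 to 12. The 74 enrolled in 10 centers are 7.4 per center so far.

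**Step 3. Evaluable participants after 20% losses.** 282 × 0.8 = 225.6; 150 × 0.8 = 120. The target is 150/282 = 53% of the requirement.

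**Step 4. Power from scaling the protocol's own requirement.** With the same effect, split and loss rate, the standardised effect grows with √N, so

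power(N) ≈ Φ[(1.96 + 0.8416)·√(N/282) − 1.96].

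For N = 150: 2.8016 × √0.5319 = 2.043; 2.043 − 1.96 = 0.083; Φ(0.083) = 0.53. If nobody were lost, the divisor is the evaluable requirement, 225.6: 2.8016 × √(150/225.6) = 2.284; 2.284 − 1.96 = 0.324; Φ(0.324) = 0.63.

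| Enrolled | Power with 20% losses | Power with no losses |
|---|---|---|
| 80 | 32% | 38–39% |
| 150 | 53% | 63% |
| 168 | 58% | 68% |

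**Step 5. Sensitivity to the unstated split.** Scaling by √N treats the null and alternative standard errors as equal, which is close to true for equal groups (about 53% at p0 = 0.733 with 60 against 60). If the groups are assumed to split 4:1 and the reference rate is again solved so that 282 gives 80%, that rate is about 77% to 80%, and power at 120 evaluable is about 44% or 58%, depending on which group is larger. The shortfall remains in every case; the 53% is not unique.

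**Step 6. Illustration only, on assumed inputs.** At an assumed 30% abstinence rate and 120 evaluable, the 95% half-width is 1.96·√(0.3 × 0.7/120) = 0.082, about 8 points, ignoring clustering by center. With an assumed 12 per center and intraclass correlation of 0.01 to 0.05, the factor √(1 + 11·ICC) makes it about 8.6 to 10.2 points. At an assumed 60/60 split and the same 30%, the RR detectable with 80% power is about 1.83.

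**The case against.** The strongest reply is that this is an observational cohort whose objectives are mainly to examine, describe, validate and predict. No single confirmatory test is named, and the article openly reports the 150. On that view the power calculation carries little weight. This tempers the consequences, but it does not make the statement true: the article still says that 282 are required and feasible, and plans tests at 5%.

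Several stronger readings are tempting, and the documents do not support them.

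- **That three sizes conflict with one another.** They do not: 150 falls within 80 to 168. The conflict is 282 against the rest.
- **That the centers cannot reach 282.** The 8 to 12 is an average, so 80 to 168 is the range planned and not a ceiling.
- **That the power shortfall belongs to a comparison of use patterns.** Statistical Methods describes four patterns, but the Sample Size section ties its 80% to no contrast, and its source RR concerns cessation under various treatments.
- **That true power is about 10%, because the Introduction cites 30% abstinence.** That is a literature figure for the first month, not the design's reference rate. Since 282 cannot arise from 30% at RR 1.20, such a figure mixes the shortfall with a separate matter, the missing basis for 282.
- **That the Catalonia denominator is simply misplaced.** The article itself places the cohort in Barcelona province in one place and in Catalonia in another. The feasibility sentence does not explain the gap, but it is not the core of the point.

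**Conclusion.** The point holds. The size stated as required is nearly twice the stated target, the site plan supports the target and not the requirement, and nothing reconciles them. The 80% power claimed for RR 1.20 is therefore not a property of the study being recruited.

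Taking 282 as the size that gives 80% power, with the same 20% losses, 150 enrolled gives about 53% and the planned range about 32% to 58%. Complete follow-up would raise 150 only to about 63%. These figures rest on accepting 282 and on simple scaling; the exact value depends on the unstated reference rate and split. That power falls short of 80% at 150 does not depend on them, because it follows from the protocol's own requirement.

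**What to change.** Make the Abstract, the Results, Eligibility for Centers and Clinicians, and Sample Size agree on one number.

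The article does not show which number governs. If 150 is the operative size, the Sample Size section should:

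- give 150 enrolled, about 120 evaluable after 20% losses;
- withdraw the 80% power claim for RR 1.20 and the feasibility sentence for 282;
- report instead the power, detectable RR or confidence-interval half-width for that size, naming the contrast, reference rate and group split as assumptions, and saying whether clustering by center is allowed for.

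The values in step 6 show the form such a statement could take; they should not be adopted unless the sponsor is prepared to defend the assumed inputs.

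If 282 is kept, the center plan and the 150 target must change to reach it, and the inputs that produce 282 should be stated.

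The first route costs wording and a less favourable stated power, with no extra participants. The second needs 282 − 150 = 132 more participants than the current target.
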